## Abstract

**Background:**

The unprecedented coverage of mobile technology across the globe has led to an increase in the use of mobile health apps and related strategies to make health information available at the point of care. These strategies have the potential to improve birth outcomes, but are limited by the availability of Internet services, especially in resource-limited settings such as Nigeria.

**Objective:**

Our primary objective is to determine the feasibility of developing an integrated mobile health platform that is able to collect data from community-based programs, embed collected data into a smart card, and read the smart card using a mobile phone-based app without the need for Internet access. Our secondary objectives are to determine (1) the acceptability of the smart card among pregnant women and (2) the usability of the smart card by pregnant women and health facilities in rural Nigeria.

**Methods:**

We will leverage existing technology to develop a platform that integrates a database, smart card technology, and a mobile phone-based app to read the smart cards. We will recruit 300 pregnant women with one of the three conditions—HIV, hepatitis B virus infection, and sickle cell trait or disease—and four health facilities in their community. We will use Glasgow’s Reach, Effectiveness, Adoption, Implementation, and Maintenance framework as a guide to assess the implementation, acceptability, and usability of the mHealth platform.

**Results:**

We have recruited four health facilities and 300 pregnant women with at least one of the eligible conditions. Over the course of 3 months, we will complete the development of the mobile health platform and each participant will be offered a smart card; staff in each health facility will receive training on the use of the mobile health platform.

**Conclusions:**

Findings from this study could offer a new approach to making health data from pregnant women available at the point of delivery without the need for an Internet connection. This would allow clinicians to implement evidence-based interventions in real time to improve health outcomes.

**Trial Registration:**

ClinicalTrials.gov NCT03027258; https://clinicaltrials.gov/ct2/show/NCT03027258 (Archived by WebCite at http://www.webcitation.org/6owR2D0kE)

## Introduction

### Background

An estimated 10% of the 2.8 million newborns who died worldwide in 2013 within 28 days of birth were born in Nigeria [1]. Most of these deaths were from diseases and conditions that are often associated with the quality of care around the time of childbirth and are readily preventable or treatable with effective interventions [2-4]. The most recent figure for under-5 child mortality in Nigeria is 124 per 1000 live births [5]. Among preventable diseases that contribute to these deaths and related morbidities are HIV and hepatitis B virus (HBV) infection and sickle cell disease (SCD), with their occurrence facilitated by health system challenges such as delays in accessing quality care. The outcome is that, despite the availability of evidence-based interventions for prevention, HIV and HBV infections and SCD remain endemic in sub-Saharan African countries [1,2,6].

Nigeria alone accounted for an estimated 26% of the global burden of new HIV infections among children [7,8]. Nigeria is one of the 22 priority countries identified by the World Health Organization that collectively account for nearly 90% of all new HIV infections among children annually [7,9]; it is one of only four countries with an HIV testing rate less than 20% among pregnant women [7]. Early identification of HIV-infected pregnant women remains a critical component of prevention of mother-to-child transmission (PMTCT) of HIV.

HBV infections remain endemic in Nigeria with liver cancer now the most common cause of cancer deaths [10,11]. The risk of perinatal transmission is higher when a pregnant woman is coinfected with HIV and HBV [11-16]. Administration of hepatitis B vaccine shortly after birth and hepatitis B immunoglobulin when available has been shown to greatly reduce the risk of perinatal transmission of HBV [15]. However, missed opportunities for prevention continue to occur in resource-limited settings; this is due to poor quality of care for at-risk pregnant women and their newborns related to lack of point-of-care diagnosis and early intervention at the time of delivery [17].

Nigeria has the highest burden of SCD in the world with an estimated 150,000 children born annually with the disease [6,18]. Despite the availability of inexpensive interventions, such as pneumococcal vaccination and penicillin prophylaxis, an estimated 50%-80% of these children with SCD suffer early death before their fifth birthday due to infections [19]. Identification of infants with SCD through newborn screening and early implementation of these simple interventions have been shown to decrease mortality.

Nigeria has developed a policy framework for introduction of critical information and communication technology (ICT) infrastructure by 2020 to support the efforts toward universal health coverage [20]. The Nigeria Federal Ministry of Health (FMOH), which provides leadership for the government’s health agency, seeks to establish and scale up innovative point-of-care tools, including mHealth solutions to improve patient care and shared use of health information. Such integrated approaches will support service delivery to HIV-infected patients and provision of primary care through agencies of government, including the National Agency for the Control of AIDS and the National Primary Health Care Development Agency. Previous efforts of the FMOH, supported by the United Nations Foundation and other partners, led to the development and ongoing implementation of a strategic project (project No. ICT4SOML) to support the scale-up of maternal and child health services in the country in order to save one million lives of women and children [21].

To effectively improve health outcomes and to avoid significant social and economic losses, a health system has to be suited to use health technology to inform early interventions [4]. However, Nigeria’s health system faces great challenges in tackling perinatal transmission of HIV and HBV and in reducing deaths among children with SCD. Major barriers to effective intervention include lack of adequate health facilities, limited access to health care providers, long distance to health facilities, transportation, and high out-of-pocket costs for patients. Other barriers, such as low perception of personal risk, poor access to testing sites, cost, confidentiality, and HIV-related stigma, have been identified to impair HIV testing and PMTCT completion in Nigeria [22].

Our initial focus on HIV, HBV, and SCD is based on several factors: (1) they are prevalent in the communities where the Healthy Beginning Initiative (HBI) was implemented; HIV prevalence among pregnant women was 2.7%, prevalence of hepatitis B surface antigen was 5%, and sickle cell trait was 23%; (2) they were identified by pregnant women, their male partners, and community leaders as conditions important to their health; (3) community screening for these conditions were well accepted during HBI implementation; (4) the integration of both communicable and noncommunicable health problems showcase the dual problem facing sub-Saharan Africa; and (5) evidence-based guidelines exist for the management of infants with SCD and infants at risk of HIV and HBV.

### Potential Opportunities to Improve Health Outcome Using Mobile Technologies

To maximize effectiveness of lifesaving interventions for maternal, newborn, and child health, available evidence suggests that such strategies should be delivered under the principle of continuum of care for mother and child, from pregnancy through birth, the newborn period, infancy, and childhood [4,23]. Yet, in resource-constrained settings like Nigeria, there are often delays in implementing lifesaving interventions due to difficulties in accessing care and problems with the quality of care provided [22]. Information gaps on maternal and child health interventions, as well as structural barriers and behavioral limitations on the demand side, hinder access to lifesaving interventions [24]. As a result, implementation of simple, cost-effective, culturally adapted, and sustainable interventions are needed to save more children’s lives [4].

### Integration of Mobile Health Technologies and Medical Decision Making

The use of mHealth with integrated data and medical decision algorithms has the potential to spread implementation of evidence-based interventions. As a marked departure from current practice, we propose integrated community-based screening and availability of data at the point of delivery using mHealth to enhance care. Nigeria is Africa’s largest mobile market with over 114 million mobile phone users and a high penetration of Internet services through mobile networks [25]. The use of mHealth is a feasible and cost-effective intervention for improving maternal and perinatal outcomes in Nigeria. It can be used to increase access to health information and reduce turnaround times for receipt of laboratory test results.

### Preliminary Studies

The HBI is a community-driven, congregation-based intervention that provides health education and on-site integrated laboratory testing—HIV plus hepatitis B and sickle cell genotype—during church-organized baby showers. In 2014, we demonstrated that the HBI was feasible, acceptable, and effective in increasing uptake of HIV, hepatitis B, and sickle cell genotype testing among pregnant women and identification of infected/affected women in southeast Nigeria (National Institutes of Health [NIH] grant No. R01HD075050) [22,26]. We subsequently demonstrated that when maternal results are made available at the point of delivery, clinicians were more likely to initiate antiretroviral prophylaxis for the HIV-exposed infant and give the first dose of hepatitis B vaccine to an infant born to a mother with hepatitis B surface antigen within 24 hours. Clinicians were also more likely to screen infants for SCD, who were born to mothers with sickle cell trait, to allow for early institution of penicillin prophylaxis and appropriate immunization. Until recently, the use of information technology to make prenatal data available at the point of delivery has been limited to high-income countries due to poor infrastructure in developing countries. Fortunately, the unprecedented spread of mobile technology has made it possible to develop mHealth platforms that can be used to provide similar services to hard-to-reach communities in resource-limited settings [23,27]. This has led to improved quality of care and decreased rate of unnecessary testing, and has allowed for early institution of evidence-based interventions that improve birth outcome [28-31].

### Our Proposal and Objectives

We propose to develop an integrated mobile health platform that is able to collect data in the community, integrate collected data into a smart card, and read the smart card using a mobile phone-based app without the need for Internet access.

Our primary objective is to determine the feasibility of developing this integrated mobile health platform. Our secondary objectives are to (1) determine the acceptability of the smart card among pregnant women and (2) determine the usability of the smart cards by the pregnant women and health facilities.

## Methods

### Ethical Consideration

This study was approved by the Institutional Review Board of the University of Nevada, Las Vegas, and the Nigerian National Health Research Ethics Committee. This study was registered with ClinicalTrails.gov (ClinicalTrials.gov identifier NCT0302725).

### Theoretical Framework

Glasgow’s Reach, Effectiveness, Adoption, Implementation, and Maintenance (RE-AIM) framework is used as a guide to assess the implementation of the mHealth platform. The RE-AIM framework offers a comprehensive approach to considering five dimensions important for evaluating the potential public health impact of an intervention [32]. The model includes the following: (1) *Reach*, the percent and representativeness of individuals willing to participate; (2) *Effectiveness*, the impact of the intervention on targeted outcomes and quality of life; (3) *Adoption*, the percent and representativeness of settings and intervention staff that agree to deliver a program; (4) *Implementation*, the consistency and skill with which various program elements are delivered by various staff; and (5) *Maintenance*, the extent to which individual participants maintain behavior change long term and, at the setting level, the degree to which the program is sustained over time within the organizations delivering it [32]. *Reach* and *Effectiveness* will assess feasibility and acceptability, while *Adoption*, *Implementation*, and *Maintenance* will assess usability and sustainability of the mHealth platform.

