#### Inclusion and Exclusion Criteria

Participants are eligible if they have a positive test result for (1) HIV, (2) hepatitis B surface antigen, and/or (3) sickle cell trait or disease, as defined by heterozygosity (AS) or homozygosity (SS), respectively, for the S variant of hemoglobin β-subunit; and (4) are residing in the local government areas where the four health facilities are situated. Those who decline to have their test results uploaded on the secure Web-based database will be excluded.

Data from the ongoing HBI will be reviewed by study staff to determine eligible participants. Trained research assistants will approach each participant independently to inform them about the study. HBI participants who consent to enroll in the study will have data collected from their community screening session stored in a secure, Web-based database. The stored data will be encrypted into a Quick Response (QR) code embedded on a *smart card* with a unique identification number printed on the outside of the card. There will be no names or any other identifiers. The smart card will be offered to each participant. The research assistants will administer a questionnaire to each participant to collect information on acceptability of the smart card. Each participant will be asked to present the smart card at prenatal visits and delivery at the selected health care facility. At the health care facility, we will identify dedicated delivery room staff that will be trained to scan the smart card and read its contents using the mobile phone app without the need for Internet connection. Mobile phones will be provided to each facility to use for the duration of the study. When a participant presents at delivery without the card, information can still be obtained from the secure, Web-based database and confirmed using the participant’s name, date of birth, and mobile phone number.

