#### Reach and Effectiveness

Reach will be calculated as the number of enrolled pregnant women relative to the number of eligible pregnant women in the study catchment area. The effectiveness will be determined by assessing the impact of the mHealth platform on key outcomes, such as screening for HIV, HBV, and sickle cell genotype and health care utilizations for follow-up visits. This will be measured by calculating the percentage of pregnant women that use the smart cards at the point of delivery, thus reducing the need for repeat testing and reducing missed opportunities for reduction of perinatal transmission of HIV and HBV and deaths among children with SCD. The reach and effectiveness of the mHealth platform will be captured through patient records and recruitment assessments.

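### Feasibility, the primary objective, is assigned to Reach and Effectiveness, but neither measures whether a card can be read offline

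*Protocol article*

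**What the plan says.** The section Our Proposal and Objectives states: "Our primary objective is to determine the feasibility of developing this integrated mobile health platform". The platform meant is one that gathers data in the community, places them on a smart card, and lets a phone app read the card offline. The Abstract's Objective gives the same capability: "read the smart card using a mobile phone-based app without the need for Internet access".

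The Theoretical Framework section divides the RE-AIM dimensions between the objectives. Reach and Effectiveness "will assess feasibility and acceptability"; Adoption, Implementation and Maintenance are given to usability and sustainability.

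The Reach and Effectiveness section then fixes the two measures:

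- Reach: "Reach will be calculated as the number of enrolled pregnant women relative to the number of eligible pregnant women in the study catchment area".
- Effectiveness: described as impact on screening and follow-up care, but measured by "calculating the percentage of pregnant women that use the smart cards at the point of delivery".
- Data source: both "will be captured through patient records and recruitment assessments".

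Offline reading appears under Inclusion and Exclusion Criteria, as a task that delivery room staff will be trained to do. It is not listed as an outcome. For a woman who arrives without her card, the same section says that "information can still be obtained from the secure, Web-based database".

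**The concern.** The feature that sets this platform apart is that a card can be written with the right data and read at delivery with no connection. A reader of the final report will look for that in the feasibility result. The article instead names two measures for feasibility, one of recruitment and one of uptake. A favourable pair of figures could be reported as evidence that the platform is feasible without any count of successful offline reads. An unfavourable card-use figure could be reported as infeasibility when the technology worked and women simply forgot the card or delivered elsewhere. A later analysis plan that followed this text would inherit the same assignment.

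**Working it through.** The plan states no figure for this point, so there is none to reproduce. The check traces the objective to its measures.

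**Step 1: Reach.** Reach = enrolled women / eligible women in the catchment area. Whether a card can be read enters neither the numerator nor the denominator. The Abstract's Results report 300 women already recruited while platform development is to be completed over 3 months. On that account the numerator is settled before the platform is finished.

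**Step 2: Effectiveness.** Define, for the women in the denominator (which the article does not specify):

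- D = proportion delivering at a study facility;
- B = proportion of those who bring the card;
- R = proportion of presented cards that the app reads correctly with no connection;
- U = the reported percentage using the card at delivery.

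The article does not define use, so take the two plausible readings.

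- *Use means the card is presented.* Then U = D × B. R does not appear, and U says nothing about it.
- *Use means a successful offline read*, the reading kindest to the plan. Then U = D × B × R, so R = U / (D × B). Because D × B is at most 1 and R is at most 1, U alone gives only U ≤ R ≤ 1. A high U would then support offline feasibility. A low U would leave R almost undetermined, because a small D or B explains it as well as a small R does.

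The named sources are patient records and recruitment assessments. No scan record or connection state is mentioned that would separate R from D and B, or show that the second reading applies.

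**Step 3: the other outcomes.**

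| Measure | Section | What it captures | Assigned to |
|---|---|---|---|
| Willingness to let staff retrieve card data | Acceptability | attitude | acceptability |
| Interviews and focus groups | Assessing Usability by Participants | barriers and support in using the card | usability |
| Delivery fidelity | Assessing Usability by Health Care Workers | whether the platform is used as planned | usability and sustainability, through Implementation |
| Think-aloud and heuristic evaluation, n = 8 | Assessing Usability by Health Care Workers | interface problems and their severity | usability |
| Concept mapping, about 60 participants | Conducting the Concept-Mapping Sessions | stakeholder views on continued use | sustainability |

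None names an offline condition, and none counts cards correctly written. Study Outcomes and Analysis has no feasibility heading. Delivery fidelity comes closest, but the article does not link it to the primary objective.

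**The case against.** The strongest defence has four parts.

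First, the objective concerns the feasibility of developing the platform, so completing a working platform is itself part of the answer. This stands. It means the offline-read proportion should not be called the plan's stated primary quantity, because the article names no such quantity. A reader might infer that the study would end with no answer at all to its primary question; the text does not support that. It does make offline reading part of the capability whose feasibility is in question.

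Second, the article describes use of the card at delivery as an offline scan by trained staff, and expects that use to reduce repeat testing, so an unreadable card would hardly count as used. This is a fair reading, and it is the second case in the check above. It turns card use into a lower bound for read success, not an estimate of it.

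Third, delivery fidelity and the think-aloud tasks would probably expose a card that fails. Probably so, but they are assigned to usability and name no offline condition.

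Fourth, a journal article leaves operational detail to the full protocol or analysis plan. That covers log fields and matching rules. It does not cover an assignment of objective to measures that the article itself makes and defines.

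A reader might also infer that the Web-database fallback would inflate the result, crediting the card with data obtained online. The text does not support this. The fallback applies to women who arrive without the card, and they fall outside the card-use numerator. Overall availability of results is not an outcome in the article. Nor does a backup for a missing card contradict offline reading of a card that is present.

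**Conclusion.** The point holds as a mismatch between the primary objective and the measures assigned to it. Reach carries no information on whether a card can be read. Card use mixes place of delivery and bringing the card with the performance of the card and app, and as worded it is not conditioned on a successful offline read. The plan as written therefore does not estimate offline-read feasibility.

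The consequence is one of interpretation, and the article gives no rates from which a numerical error could be derived. On the kindest reading of use, the card-use figure places the offline-read rate between that figure and 100%; if use means only presentation, it places no limit. The conclusion rests on the definitions in the Reach and Effectiveness section being the operative ones, and on no scan-level measure being assigned to feasibility elsewhere in the article.

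**What to change.** In Theoretical Framework and in Reach and Effectiveness, add as the main feasibility measure the proportion of cards presented at delivery that the app decoded without a data connection and that returned the record stored for that card number. Alongside it, report the proportion of consented records correctly written to a card. Take the read result from an automatic scan log in the app: card number, time, connection state and decode result. Keep Reach and card use as separate measures of uptake. Report Web-database look-ups for women without a card as a separate count.

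No extra participants are needed. As an illustration with assumed counts, 285 correct reads of 300 cards presented gives 95% (Wilson 95% CI 92% to 97%). If only 90 cards were presented, 86 correct reads gives 96% (89% to 98%). Both intervals ignore clustering within the four facilities, and the first assumes that every woman presents her card.

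The cost is a small programming task in an app still under development, some rewording of outcomes, and a feasibility figure that may be less favourable than the uptake figures.
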